### Design

This is a prospective, open-label, randomized controlled, multicenter clinical study with two arms. Eligible patients are first screened by safety laboratory testing. Patients with diagnosed mild/general COVID-19 infection are randomized to the following two arms at a 1:1 ratio:
Arm 1 (control arm): lopinavir/ritonavir treatment for diagnosed mild/general COVID-19 infection uses lopinavir 800 mg/day and ritonavir 200 mg/day for no more than 10 daysArm 2 (investigation arm): chloroquine phosphate treatment using chloroquine phosphate 1000 mg/day, equivalent to chloroquine 600 mg/day for no more than 10 days

The CRF is shown in Fig. 1. The schedule of treatment visits and data collection (also known as the CRF) is shown in Table 1.

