**Table 1 Tab1:**
[figure not shown]
The schedule of treatments and data collection

The *SOFA (Sequential Organ Failure Assessment) score* predicts mortality risk for patients in the intensive care unit based on laboratory results and clinical data^1^

*Coagulation index*: *PT* prothrombin time, *APTT* activated partial prothrombin time, Fib fibrinogen, *D-Dimer* D-dimer, *PLT* platelet count

*Inflammatory factors*: various cytokines involved in inflammation, such as interleukin (IL)-6, IL-10, tumor necrosis factor (TNF)-α, etc.

*PCT (procalcitonin)*: a protein that increases when severe bacterial, fungal, and parasitic infections, sepsis, and multiple organ failure occur

− D0: before the research; D0: start of the research; D1: 1st day of the research; D2: 2nd day of the research; D3: 3rd day of the research; D4: 4th day of the research; D5: 5th day of the research; D6: 6th day of the research; D7: 7th day of the research; D10: 10th day of the research; D14: 14th day of the research; D21: 21st day of the research; D28: 28th day of the research; D29: after the research

References:

1 Medlej K. Calculated decisions: sequential organ failure assessment (SOFA) score. *Emerg Med Pract* 2018;20:CD1-CD2.

Researchers will evaluate treatment adherence during each visit. If a scheduled visit is delayed or cancelled, the research team will contact the participant at once. No treatment or intervention is prohibited for any of the participants.

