### Definitions

#### The clinical recovery time and adverse events

We define the clinical recovery time as the time (in hours, no more than 28 days) from the start of study drug intervention to normalization of body temperature, respiratory symptoms (cough, nasal stuffiness, nasal discharge, etc.), respiratory frequency, and blood-oxygen saturation. Specifically, also meeting the following criteria at the same time:
① No fever: axillary body temperature ≤ 37.2 °C② Relief of respiratory symptoms (72 consecutive hours)③ Respiration rate ≤ 24/min (resting state)④ Fingertip blood oxygen > 94%

Adverse events (AEs) refer to adverse medical events that occur after a patient or clinical trial participant receives a drug, but they are not necessarily causally related to treatment.

Serious adverse events (SAEs) refer to events that require hospitalization, prolonged hospital stay, disability, affect working ability, are life-threatening or fatal, cause congenital malformation and other events that occur during the clinical trial.

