### Limitations

Randomized controlled studies still have some design limitations. First, the sample size we use is relatively small and the 28-day treatment period is short. Therefore, we will not be able to estimate possible relapses of pneumonia after long-term treatment. Second, the pathophysiology of novel coronavirus pneumonia has not been elucidated. As only clinician assessment is used (including lung computed tomography (CT) results and count of viral load), there is no objective indicator to judge the effect of treatment on COVID-19 infection. Finally, the follow-up period in this study was relatively short. In light of these limitations, we will develop a more reasonable treatment cycle and follow-up period to explore the efficacy of chloroquine in patients with COVID-19.

We also know that there will be many biases in the open trial, and we have taken a number of measures to control the possible bias in the trial, as follows:

(1) Strict exclusion criteria are formulated to effectively control other confounding factors that may affect the efficacy; (2) the trial uses random grouping to ensure that the two groups of patients are comparable; (3) before the patient signs the informed consent form, the researchers and the patients make full communication to ensure that the patients understand the entire trial content, and try to eliminate the impact of the patient’s psychological state on the trial effect; (4) the main and secondary indicators for evaluating the efficacy are objective indicators to avoid the influence of subjective factors; (5) before the start of the trial, the researchers will conduct unified system training to ensure the uniformity and correctness of data collection and index evaluation.

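### The primary endpoint accepts temperature and oxygen readings taken under antipyretics or supplemental oxygen, so in this open-label trial arm-dependent supportive care can bring forward some recorded recoveries

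*Protocol article*

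**What the plan says.** Under Definitions (the clinical recovery time and adverse events), the protocol article measures the primary endpoint in hours, up to 28 days, "from the start of study drug intervention to normalization of body temperature" and of respiratory symptoms, respiratory frequency and blood-oxygen saturation. It then requires "also meeting the following criteria at the same time":

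1. "No fever: axillary body temperature" at most 37.2 °C
2. "Relief of respiratory symptoms (72 consecutive hours", in brackets
3. respiration rate at most 24/min, at rest
4. "Fingertip blood oxygen" above 94%

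Only respiration carries a measurement condition (rest). Only the symptom criterion carries a printed duration.

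The Design section adds, after the visit schedule: "No treatment or intervention is prohibited for any of the participants". It also states: "This is a prospective, open-label, randomized controlled, multicenter clinical study with two arms". The Statistical analysis section gives primary weight to the intention-to-treat set. It removes patients who received treatment that could affect the efficacy evaluation from the per-protocol set only, and does not list those treatments. Among its measures against open-label bias, the Limitations section says that "the main and secondary indicators for evaluating the efficacy are objective indicators to avoid the influence of subjective factors".

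**The concern.** A thermometer or oximeter reading is objective, but antipyretics and oxygen can change it, and here they are given by staff who know the allocation. If the two arms receive this care at different rates, patients in one arm may reach the temperature or oxygen threshold earlier without any difference in the disease. The log-rank test would count that as a treatment effect. Calling the indicators objective, as the Limitations section does, gives no protection against this route.

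The secondary outcome, time to return to normal temperature, has no separate definition. If it uses the same 37.2 °C threshold, no second criterion stands behind it and it is more exposed than the primary endpoint.

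**Working it through.** **The plan's own figure.** The Sample size section gives medians of 8 and 4 days (hazard ratio 2.0), two-sided α = 0.05, 78 events and 112 patients. I read its 85% as power.

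- Schoenfeld power: Φ(√78 × ln 2 / 2 − 1.96) = Φ(3.06 − 1.96) = Φ(1.10) = 86.5%.
- Events needed for 85% power: 75 (Schoenfeld) or 81 (Freedman). The stated 78 lies between them.

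The figure is reproduced closely enough and is not in dispute. The point concerns what is counted as an event.

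**What the text permits, criterion by criterion**

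| Criterion | Condition on the reading | Printed duration | Can support alter it? |
|---|---|---|---|
| Temperature | none | none | yes, antipyretics |
| Respiratory symptoms | none | 72 hours | yes, symptomatic medication |
| Respiration rate | at rest | none | not examined here |
| Oxygen saturation | none (room air not required) | none | yes, supplemental oxygen |

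All four must hold together. A reading under support therefore advances the clock only if the patient's last unmet criterion is temperature or oxygen.

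**Illustration of size.** The documents give no rate of antipyretic or oxygen use, so every usage figure here is an assumption. The setting is 56 per arm, exponential recovery times, censoring at day 28 and a two-sided log-rank test at 5%. There is no true difference (both medians 8 days), and a share of each arm has recovery recorded k days early. Where separate runs of the simulation differed, the range is given.

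| Affected, arm A / arm B | k (days) | Rejection rate | If temperature or oxygen is limiting in only half |
|---|---|---|---|
| none | – | about 5% | – |
| 50% / 20% | 2 | 5.9% to 6.3% | about 5% |
| 50% / 20% | 3 | 6.9% to 7.2% | about 6% |
| 60% / 20% | 3 | 8.2% to 8.9% | about 6% |

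The induced difference in mean recorded time is at most gap × k: 0.30 × 2 = 0.6, 0.30 × 3 = 0.9 and 0.40 × 3 = 1.2 days. The planned effect is 4 days in the median, or (8 − 4)/ln 2 = 5.8 days in the mean under exponential times. The distortion is small beside that effect.

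**A harsher assumption.** Suppose support halves the recorded time, with 30% affected in one arm. Rejection is then about 6%, 10%, 16% and 28% when 40%, 50%, 60% and 70% are affected in the other arm. The result depends heavily on assumptions that the documents cannot settle.

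**Equal use in both arms, hazard ratio 2.0.** With every patient followed to day 28 there are about 107 events, 56 × (0.912 + 0.992), so baseline power is about 94% rather than the 86.5% at 78 events. With 20% to 60% of both arms affected, power stays at 93% to 94% under the k-day model and falls to 92% to 89% under the halving model. Differential use is the risk that matters.

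**The case against.** The strongest reply is that the definition already limits the problem. A reader might infer that a pneumonia patient at 95% on nasal oxygen and 37.0 °C after an antipyretic counts as recovered at that hour. The text does not support this: that patient must also have had respiratory symptoms relieved for 72 hours and a resting respiration rate of at most 24/min. Where cough or nasal symptoms outlast fever, antipyretic use need not move the clock at all. So it is also wrong to infer that any arm difference in supportive care shifts the endpoint. This part of the objection stands.

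A reader might also infer that one qualifying set of readings is enough for the other three criteria. That is one reading. The definition speaks of normalization in all four domains with the criteria met together, so the 72 hours may have been meant more widely. The text is ambiguous. Even a 72-hour rule for every criterion would not exclude 72 hours of continuous support.

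Three further points are fair. Oxygen use may be limited in mild disease. The documents do not suggest that use differs by arm. The visit schedule and case report form are not shown and may already record such use.

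Two replies do not carry. The per-protocol restriction is secondary and unspecified, and leaves the intention-to-treat analysis unprotected; it also sits awkwardly beside a rule that prohibits nothing. Nor is the gap merely an effect of condensing the protocol into an article: the article prints thresholds and one measurement condition, and states the permissive rule outright.

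**Conclusion.** The point holds in a limited form. As printed, the temperature and oxygen criteria can be met under treatment that normalises them, nothing is prohibited and care is unblinded. Arm-dependent supportive care can therefore advance recorded recovery in patients whose last unmet criterion is one of those two.

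Under assumed arm gaps of 30 to 40 points and advances of 2 to 3 days, the 5% test rejects at about 6% to 8 or 9%. It rejects at about 6% or below if those criteria are limiting in only half of the affected patients. These figures are illustrative: they rest on exponential times and invented usage rates.

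The stronger claim that equal use seriously dilutes a real effect is not supported, because power remains above the planned 85% under both models examined. Nor do the documents show that bias has occurred. This should be fixed, but it is not a fatal flaw.

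**What to change.** In the endpoint definition:

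- Count a temperature reading only if no antipyretic was taken within a fixed preceding window, with its length stated in advance.
- Count a saturation reading only if taken on room air.
- State which criteria the 72 hours cover, and whether recovery is dated to the start or the end of that period.
- Apply the antipyretic condition to time to return to normal temperature.
- Record antipyretic and oxygen use with each reading, if the case report form does not already do so.

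The per-protocol rule and the statement that nothing is prohibited should also be reconciled, by listing which treatments count as affecting the efficacy evaluation.

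This changes what counts as recovery, not the care that any patient may receive. No sample-size figure changes as a direct result.

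The costs are real but modest. Recorded recovery times become somewhat longer, and patients on continuous support count as not yet recovered. The Trial status section says that randomization began in February 2020 and that recruitment was ongoing, so antipyretic timing may be incomplete for patients already enrolled. The definition should therefore be settled before any comparison by arm, with the currently printed definition kept as a sensitivity analysis.

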### Outcomes

The primary outcome is the clinical recovery time of no more than 28 days after the completion of therapy and follow-up. The secondary outcomes include the rate of treatment success after the completion of therapy and follow-up, the time of treatment success after no more than 28 days, the rate of serious adverse events (SAEs) during the completion of therapy and follow-up, and the time to return to normal temperature (calculated from the onset of illness) during the completion of therapy and follow-up.

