#### Analysis of secondary outcomes

The analysis of secondary outcomes will be described as explorative outcomes. The rate of treatment success after the completion of therapy and follow-up among the two groups will be compared using the chi-square test or Fisher’s exact test. The time of treatment success after no more than 28 days, the time to normal temperature (calculated from the onset of illness) during the completion of therapy and follow-up will be calculated in each group and compared using the log-rank test.

The rate of SAEs during the completion of therapy and follow-up will be compared among the two groups using the chi-square test or Fisher’s exact test.

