## Discussion

As of 10 April 2020, the total number of COVID-19 infection diagnoses in the world was more than 1.3 million, with more than 80,000 deaths (https://www.who.int/dg/speeches/detail/the-cooperation-council-of-the-turkic-speaking-states%2D%2D-10-april-2020). There is no known curative treatment for COVID-19, neither novel treatments nor vaccines. Cao’ study observed no benefit with lopinavir/ritonavir treatment in severe COVID-19 patients [19]. Lim’s study observed that the beta-coronavirus viral load significantly decreased with no or little coronavirus titers after administering lopinavir/ritonavir [2]. Gautret’s study [20] concluded that chloroquine is significantly associated with viral-load reduction/disappearance in COVID-19 patients. In the seventh edition of the Chinese version of the COVID-19 Diagnosis and Treatment Plan (http://www.nhc.gov.cn/yzygj/s7653p/202003/46c9294a7dfe4cef80dc7f5912eb1989/files/ce3e6945832a438eaae415350a8ce964.pdf), the recommended antiviral drugs are lopinavir/ritonavir, chloroquine phosphate and other drugs.

The Chinese have decreased the current epidemic situation in China by using the recommended drugs. The relief of the epidemic in most provinces of China has at least confirmed the effectiveness of the treatment to a certain extent, but further strong and effective, evidence-based data is needed.

The trial will be conducted in a clinical outpatient and inpatient setting by experienced clinicians, and participants will be recruited from the patient base of the other three hospitals participating in the trial. The purpose of this prospective, open-label, multicenter randomized controlled, comprehensive clinical study is to evaluate the efficacy and safety of chloroquine phosphate and lopinavir/ritonavir in patients with mild/general COVID-19 infection. The results of this study should provide meaningful information and evidence for clinical practice and should help to design a proven and reasonable RCT soon.

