## Abbreviations

ACE2: Angiotensin-converting enzyme 2
AE: Adverse event
COVID-19: Corona Virus Disease-2019
CI: Confidence interval
CRF: Clinical research flowchart
CTCAE: Common Terminology Criteria for Adverse Events
HCoVs: Human corona viruses
HIV: Human immunodeficiency virus
ITT: Intention-to-treat
MAPK: Mitogen-activated protein kinase
PP: Per-protocol
RT-PCR: Reverse transcription polymerase chain reaction
S protein: Spike protein
SAE: Severe adverse event
SARS-CoV: Severe Acute Respiratory Syndrome Corona Virus

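### The SAE definition closes with an unqualified catch-all and includes a work-ability item with no threshold, so it does not mark off serious from ordinary adverse events

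*Protocol article*

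**What the plan says.** All references are to the protocol article.

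- **Definitions, The clinical recovery time and adverse events.** An adverse event (AE) is an adverse medical event after receipt of a drug, with the reservation "but they are not necessarily causally related to treatment". The next sentence opens "Serious adverse events (SAEs) refer to events that require hospitalization, prolonged hospital stay, disability" and goes on to "affect working ability, are life-threatening or fatal, cause congenital malformation and other events that occur during the clinical trial".
- **Outcomes.** One of the secondary outcomes is "the rate of serious adverse events (SAEs) during the completion of therapy and follow-up". The other secondary outcomes named there concern efficacy.
- **Analysis of secondary outcomes.** "The analysis of secondary outcomes will be described as explorative outcomes". For safety, a chi-square or Fisher's exact test compares the SAE rate between the arms.
- **Safety assessment.** All AEs are collected under CTCAE. How severe an event is, whether it is serious, and whether it is related to the drug are treated as three separate features. The arms are compared on AEs by drug relationship and by severity.
- **Abbreviations.** The list gives "SAE: Severe adverse event", while the Abstract, Outcomes and Definitions use the word serious.

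**The concern.** An SAE definition has to exclude something. Here two of the listed items exclude little or nothing. The closing item admits whatever happens during the trial. The work-ability item admits any event that interferes with work, however slight or brief. Eligible patients have fever, cough or fatigue by the inclusion criteria, so ordinary illness can bear on ability to work.

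This matters because the SAE rate carries the safety side of the named secondary outcomes and is tested between arms. Treatment allocation is known, and four hospitals apply the definition. Where the text gives no threshold, each site must supply its own, and it can do so knowing the arm. The count could then be inflated with ordinary events, or could differ between sites or arms for reasons other than serious harm.

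**Working it through.** **1. Sort the listed items.** The definition names eight: hospitalization, prolonged stay, disability, effect on work, life-threatening, fatal, congenital malformation, and other events in the trial. Six are recognised seriousness criteria. Two are open: effect on work (no degree or duration) and other events (no qualifier at all).

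**2. Apply the closing item literally.** Let A be the set of AEs and S the set of SAEs. The SAE sentence follows the AE definition and is naturally read as describing a subset, so S lies within A. The closing item admits every event in the trial, so A lies within S. Together these give S = A. Safety assessment uses seriousness as a feature that some AEs have and others lack, which requires S to be smaller than A. The literal reading therefore conflicts with the document's own use of the term.

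**3. Apply it charitably.** Read the closing item as meaning other events of the same kind. S is then smaller than A, but the text does not say how comparable an event must be. The boundary is left to the reader at each of the four hospitals.

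**4. Check the abbreviation.** Severe appears for SAE only in the abbreviation list. Safety assessment keeps severity and seriousness apart, so by the document's own usage the list entry is a slip. It does not change the definition.

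**5. Size.** The article gives no expected SAE rate, difference or power, so there is no stated figure to reproduce. The following is an illustration only. From the article: 56 per arm and a two-sided 5% level. Assumed: true serious-event rates of 5% and 20%, and a share b of patients in *both* arms with a non-serious event counted as an SAE, independently of the serious ones.

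Observed rate = 1 − (1 − p)(1 − b). Power = Φ[(Δ − 1.96·s₀)/s₁], where Δ is the difference in observed rates, s₀ its pooled standard error and s₁ its unpooled standard error.

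For b = 0: s₀ = √(2 × 0.125 × 0.875/56) = 0.0625; s₁ = √((0.0475 + 0.16)/56) = 0.0609; (0.15 − 0.1225)/0.0609 = 0.45; power 67%.

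For b = 0.2: the rates are 1 − 0.95 × 0.8 = 0.24 and 1 − 0.80 × 0.8 = 0.36; s₀ = 0.0866; s₁ = 0.0859; (0.12 − 0.1697)/0.0859 = −0.58; power 28%.

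| b | Observed rates | Power (5% vs 20%) | Power if 5% vs 25% |
|---|---|---|---|
| 0 | 5% vs 20% | 67% | 85% |
| 0.2 | 24% vs 36% | 28% | 44% |
| 0.4 | 43% vs 52% | 16% | 24% |
| 0.6 | 62% vs 68% | 10% | 14% |

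The observed rates in the second column belong to the 5% vs 20% case. Dilution alone, with no bias between arms, can hide a real difference. How far it does so depends on how sites apply the wording, which the article does not show.

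**The case against.** The strongest defence is that the definition is clumsy but workable. SAEs are naturally a subset of AEs, six of the items are standard, and the last phrase can be taken as shorthand for other events of that kind. Safety assessment makes sense only on that reading. The article also compares AEs by drug relationship and by severity, so related and severe harm is examined whatever the SAE count does. The secondary outcomes are labelled exploratory.

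Most of this stands, and it limits the point to ambiguity and possible inflation. It does not supply the missing threshold. Nor can the gap be put down to condensation in a journal article, because the article prints the definition.

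Four stronger readings are tempting, and the documents do not support them.

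- *The SAE rate does not measure serious drug harm.* The list does contain recognised criteria. Drug causation is also the wrong test, because the AE definition does not require it and relationship to drug is analysed separately.
- *Slow recovery alone counts as an SAE, so the slower arm collects more.* From the planned medians of 8 and 4 days and exponential times, a reader might compute 2^(−10/8) = 42% and 2^(−10/4) = 18% unrecovered at day 10, or about 24 against 10 of 56. The arithmetic is right. The inference assumes that every such patient is scored as an SAE and that the planned benefit is real. On the natural reading the adverse event must itself require the stay. Day 10 is the longest treatment duration; nothing links it to length of stay.
- *Sites work with two event sets because of the abbreviation list.* Nothing shows that they use it.
- *The monitoring board would be misled.* Its data review is not described as resting on an SAE count.

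Operational rules for isolation stays or for the index illness may sit in the full protocol, which is not shown. Their absence here is no finding.

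**Conclusion.** The point holds as a defect in a stated definition. Read as written, it erases the line between AE and SAE; read charitably, it leaves the line for each site to draw. The affected quantity is a named, tested, exploratory secondary outcome and the only safety measure among the secondary outcomes. The likely effects are inflation and uneven scoring by site or arm. No direction of bias can be predicted from the documents, and the size rests wholly on assumed rates and assumed site behaviour. The primary analysis is unaffected, and the planned AE comparisons by relationship and severity soften the consequence. The abbreviation entry is editorial. Correction is worthwhile because it is specific and cheap.

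**What to change.** In Definitions:

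- State that an SAE is an adverse event that meets at least one of the listed seriousness criteria.
- Replace the catch-all with *other medically important events of comparable seriousness*.
- Limit the work-ability item to persistent or significant incapacity, or delete it.
- Make clear that the adverse event itself must cause the admission or the prolonged stay.

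In Abbreviations, change the expansion of SAE to *serious adverse event*.

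The cost is definition wording and site retraining. Recruitment was under way at publication, so events already recorded should be reclassified from the case report forms under the closed definition. The one downside is a lower reported SAE count.
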